#### Strategies to improve adherence to interventions {11c}

Patients will be educated about the possible risks of non-adherence. Treatment adherence will be assessed at regular intervals using the Medication Adherence Report Scale (MARS) questionnaire [35].

#### Relevant concomitant care permitted or prohibited during the trial {11d}

Concomitant care with long-term antibiotic prophylaxis is not permitted, except for rifaximin prescribed for hepatic encephalopathy. Patients will be stratified according to their use of rifaximin at randomisation and whether they are presently on the waiting list for a liver transplant. As hyperkalaemia is a known potential side effect of co-trimoxazole, caution will be taken in patients taking other medications that can cause hyperkalaemia: ACE inhibitors, angiotensin receptor blockers, and potassium-sparing diuretics. Patients at increased risk of renal dysfunction and/or hyperkalaemia, namely those with existing kidney dysfunction and those taking spironolactone or amiloride, are not eligible if the PI judges this risk cannot be managed with the adjustment of diuretics.

#### Provisions for post-trial care {30}

Other medical care during and post-trial will be standard medical care.

### Outcomes {12}

The primary outcome is overall survival during follow-up.

The secondary outcomes are as follows:Time to the first incidence of SBPHospital admission rates at 18 monthsIncidence of *C. difficile*-associated diarrhoea at 18 monthsIncidence of infections other than SBP with hospital admission at 18 monthsIncidence of other cirrhosis-related events (e.g. variceal haemorrhage) at 18 monthsIncidence of renal dysfunction with creatinine > 133 µmol/L (1.5 mg/dL) at any point during hospital admissionIncidence of anti-microbial resistance at 18 monthsIncidence of liver transplantation at 18 monthsWe will explore the potential impact of alcohol cessation and recidivism rates in those with alcohol as a cause of cirrhosis and any interaction with treatmentProgression of liver disease assessed by an increase in Model for End-Stage Liver Disease (MELD) score between baseline and end of trial follow-upSafety and treatment-related serious adverse eventsTreatment adherence (assessed by MARS questionnaire)Incidence of resolution of ascites with diuretic treatment not required for 6 months at 18 monthsIncidence of transjugular intrahepatic portosystemic shunt (TIPS) insertion at 18 monthsHealth-related quality of life assessed using the EQ-5D-5L QuestionnaireHealth and social care resource use assessed using Hospital Episode Statistics (HES) databaseMean incremental cost per quality-adjusted life year (QALY) gained

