### Eligibility criteria {10}

The inclusion and exclusion criteria for patient eligibility are listed in Table 1.

**Table 1 Tab1:** Eligibility criteria for ASEPTIC trial

Inclusion criteria	Exclusion criteria
Patients with cirrhosis of Child–Pugh class B or C and the presence of ascites requiring any diuretic treatment or at least one or more paracentesis within 3 months prior to enrolment	Patients with current or previous SBP (defined as ascitic polymorphonuclear count > 250 cells/mm^3^ with either positive or negative ascitic fluid culture without an evident intra-abdominal surgically treatable source of infection; a white cell count > 500 cell/mm^3^ or positive microbial culture may be considered as evidence of previous SBP if the site PI considers this was in the context of a likely clinical diagnosis of SBP)
At least 18 years of age	Patients receiving palliative care with an expected life expectancy of < 8 weeks
Documented informed consent to participate	Allergy to co-trimoxazole, trimethoprim, or sulphonamides
	Pregnant or lactating mothers
	Patient enrolled in a clinical trial of investigational medicinal products (IMPs) that would impact their participation in the study
	Patients with serum potassium > 5.5 mmol/L related to pre-existing kidney disease which cannot be reduced^a^
	Patients receiving antibiotic prophylaxis (except rifaximin)^a^
	Patients with long-term ascite drains^a^
	Women of child-bearing potential and males with a partner of child-bearing potential without effective contraception for the duration of the trial treatment
	Patients with pathological blood count changes^a^: haemoglobin < 70 g/L, granulocytopaenia defined as absolute neutrophil count < 500 cells/µL, and/or severe thrombocytopaenia with platelets < 30 × 10^9^/L
	Patients with severe renal impairment, with eGFR < 15 mL/min
	Patients with skin conditions: exudative erythema multiforme, Stevens-Johnson syndrome, toxic epidermal necrolysis, and drug eruption with eosinophilia and systemic symptoms
	Patients with congenital conditions: congenital glucose-6-phosphate dehydrogenase deficiency of the erythrocytes and haemoglobin anomalies such as Hb Köln and Hb Zürich
	Patients with acute porphyria
	Any clinical condition which the investigator considers would make the patient unsuitable for the trial

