^c^Blood tests should include full blood count, with haemoglobin, white cell count, platelets, INR (or prothrombin time converted to INR), sodium, potassium, serum creatinine, and urea. Liver function tests should include albumin, alanine aminotransferase (ALT), alkaline phosphatase, and bilirubin. Renal function tests including eGFR

^d^At each indicated visit, one bottle of 100 capsules of trial medication is dispensed to the patient (either co-trimoxazole or placebo capsules)

^e^Visit 2 is to monitor the safety of the patient and to make any dose modifications to concomitant medications if needed

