#### Sample size {14}

For overall survival as the primary outcome, we anticipate a hazard ratio (HR) of 0.62 and calculated that 432 patients will be required to generate 187 events, incorporating a 10% cumulative probability of loss-to-follow-up by the end of the study. Guided by the Kaplan–Meier 18-month survival estimate amongst patients with cirrhosis and ascites in the control arm of the ANSWER trial [30], and assuming an exponential survival distribution, we anticipate 66% survival in the control arm at 18 months. In the experimental arm, we expect 77% of patients surviving at 18 months. The recruitment will be uniform over a period of 2.5 years, and the follow-up time will be 18 months minimum with a maximum potential follow-up of 48 months. This calculation was based on a two-sided 5% type 1 error rate and 90% power. The primary event rate overall (blinded to allocation) will be monitored by the trial steering committee, and follow-up may be extended beyond the planned period to achieve the required number of events, with any extension agreed with the funder. Disruption to the trial schedule owing to the COVID-19 pandemic may necessitate an extension of the recruitment period.

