## Statistical methods

### Statistical methods for primary and secondary outcomes {20a}

A detailed statistical analysis plan will be written prior to the first unblinded analysis and approved in advance by the trial steering committee. The main analyses will be conducted following the intention-to-treat principle. For the primary outcome, Kaplan–Meier survival curves will be compared using the log-rank test, according to the allocated treatment in an intention-to-treat manner. An unadjusted Cox proportional hazards model will be fitted, and the unadjusted hazard ratio and 95% confidence interval will be presented. An adjusted Cox model will then be fitted, adjusting for the stratification factors (active participation on the liver transplant waiting list, rifaximin prescription at enrolment, alcohol as a cause of cirrhosis, and active alcohol consumption at randomisation if the amendment submitted in June 2022 is successful) by including them as covariates in the model. All statistical tests will use a two-sided *p*-value of 0.05.

If there is evidence of non-proportional hazards, the life expectancy difference and life expectancy ratio between the two arms will be presented [36]. The stratified log-rank test will be reported in this instance as well, and the odds ratio for death at 18 months will be calculated using logistic regression.

Binary secondary outcomes will be analysed using logistic regression, and continuous outcomes using linear regression adjusting for baseline values (i.e. ANCOVA). Time to the first incidence of SBP will be presented with Kaplan–Meier curves and compared between the arms using the log-rank test. Serious adverse event rates will be presented by treatment arm and grade. Quality of life scores will be compared using a hierarchical linear regression model.

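### The in-hospital renal dysfunction outcome has no baseline condition, so stable pre-existing kidney impairment is counted as incident and dilutes the treatment comparison

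*Protocol article*

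**What the plan says.** The outcome list (Protocol article, Outcomes {12}) includes the incidence of "renal dysfunction with creatinine > 133 µmol/L (1.5 mg/dL) at any point during hospital" admission. The threshold, units and setting are fixed. No normal baseline, minimum rise or repeat value is required. In the same list, progression by MELD score is defined as a change from baseline.

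On entry, Table 1 (Eligibility criteria {10}) excludes "Patients with severe renal impairment, with eGFR < 15 mL/min", and also "Patients with serum potassium > 5.5 mmol/L related to pre-existing kidney disease which cannot be reduced". The concomitant care section {11d} adds that patients at raised risk of renal dysfunction or hyperkalaemia, including those with existing kidney dysfunction, "are not eligible if the PI judges this risk cannot be managed with the adjustment of diuretics". None of these sets a creatinine limit.

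Baseline renal data exist. Table 2 schedules blood tests at screening, and its footnote lists "sodium, potassium, serum creatinine, and urea" and "Renal function tests including eGFR".

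On analysis, section {20a} states: "Binary secondary outcomes will be analysed using logistic regression, and continuous outcomes using linear regression adjusting for baseline values". Baseline adjustment is attached to continuous outcomes only.

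**The concern.** The outcome is named an incidence, but the rule measures whether a patient is above a level at some moment in hospital. Anyone already above that level at randomisation, and stable, meets it at the first inpatient test. Such a patient says nothing about the treatment, yet enters both numerator and denominator of the arm.

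This would have two effects: the reported frequency of renal dysfunction would be too high, and the odds ratio would be pulled towards 1. The second matters because the protocol treats renal dysfunction as a risk to be managed on trial medication, and dilution is unwelcome in an outcome that could show harm. A lesser issue is that one value just over the line suffices, so a patient stable slightly below 133 µmol/L can be scored on ordinary variation if tested often enough.

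**Working it through.** **The plan's own figures.** No rate, effect or power is stated for the renal outcome. The only design calculation concerns survival, where "we anticipate a hazard ratio (HR) of 0.62". It reproduces: Schoenfeld events = 4(1.960 + 1.282)²/(ln 0.62)² = 184, and Freedman's formula gives 191, against the stated 187. With 66% control survival at 18 months, uniform 30-month accrual, 18–48 months of follow-up and 10% loss by month 48, 432 patients yield 187 events. It has no bearing on this point.

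**Step 1: does eligibility overlap the event threshold?** 133/88.4 = 1.50 mg/dL, so the two stated units agree. The article names no eGFR equation; CKD-EPI 2009 is assumed here. Above the knot κ (0.9 mg/dL for men, 0.7 for women),

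eGFR = 141 × (Scr/κ)^−1.209 × 0.993^age (× 1.018 for women).

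- Man aged 60: 141 × (1.5045/0.9)^−1.209 × 0.993^60 = 49.7.
- Woman aged 60: 141 × (1.5045/0.7)^−1.209 × 0.993^60 × 1.018 = 37.3.
- Ages 45, 60 and 70: men 55, 50, 46; women 41, 37, 35.

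A creatinine of 133 µmol/L thus corresponds to an eGFR of about 35–55. A patient with stable eGFR from 15 up to that value passes the numeric entry limit and already exceeds the outcome threshold.

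**Step 2: how much dilution?** The documents give neither the share of such patients nor admission or renal event rates, so everything in this step is an assumption:

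- 216 per arm (432 allocated 1:1);
- 70% of patients admitted;
- new events in 20% (control) v 12% (active) of those admitted;
- a share q in each arm already above 133 µmol/L, scored whenever admitted.

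Event probability as written: p = 0.7q + (1 − q) × 0.7 × r, with r = 0.20 or 0.12.

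Power (Wald test on the log odds ratio): Φ(|ln OR|/SE − 1.96), with SE² the sum of the reciprocals of the four expected cell counts. For new cases only, n = 216(1 − q) per arm and the event probabilities are 0.140 v 0.084, so OR = (0.084/0.916)/(0.140/0.860) = 0.56 at every q.

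Worked case, q = 5%:

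- control 0.035 + 0.95 × 0.140 = 0.168;
- active 0.035 + 0.95 × 0.084 = 0.115;
- OR = 0.64, SE = 0.280, power = 35%;
- pre-existing cases are 0.035/0.168 = 21% of control events and 0.035/0.1148 = 30% of active-arm events.

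| q | Control v active, as written | OR as written | Power, new cases only | Power as written |
|---|---|---|---|---|
| 2% | 15.1% v 9.6% | 0.60 | 44% | 40% |
| 5% | 16.8% v 11.5% | 0.64 | 43% | 35% |
| 7.5% | 18.2% v 13.0% | 0.67 | 42% | 31% |
| 13% | 21.3% v 16.4% | 0.73 | 40% | 25% |

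**Step 3: single values.** Assume a true stable creatinine of 120 µmol/L, within-person variation of 5–8% and independent errors. One test exceeds 133 with probability 1 − Φ(13/6.0) = 1.5% to 1 − Φ(13/9.6) = 9%. With three tests, at least one does so in 4.5–24% of admissions.

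**The case against.** Several counter-arguments carry weight.

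- **Entry is tighter than the eGFR limit alone.** The potassium exclusion and the investigator's judgement under {11d} remove some patients with kidney disease. This stands, and it is why the table starts at 2%. It does not close the gap, because neither criterion limits creatinine.
- **The size is assumed throughout.** This stands. At the low end the loss is modest (power 44% to 40%). Even the cleaner definition has power below 50% here, so the outcome may be inconclusive either way.
- **An analysis plan may settle it.** The article defers detail to one, and handling of patients abnormal at baseline could be fixed there. But the article states an operational rule, and that rule as written counts these patients. This is more than a detail left open.
- **Low stakes.** This is one of a long list of secondary outcomes. Renal function is also followed through scheduled blood tests, eGFR-triggered adjustment of trial medication and adverse event reporting.
- **A baseline rule has its own errors.** Screening may be up to 12 weeks before randomisation, and inpatients can be recruited shortly before discharge, so the screening value may be transiently abnormal. In acutely admitted patients, a single high value may also be genuine renal dysfunction.

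A reader might go further and infer that the definition biases the comparison in one direction, or that it would conceal any renal benefit or harm. The documents do not support that. Pre-existing disease is balanced on average by randomisation, so the result is attenuation, and renal safety is observed by other routes. Nor do they state that fewer renal events are an expected benefit; the discussion speaks only in general terms of infection leading to organ failure and death.

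**Conclusion.** The point holds as a badly fixed definition of one secondary outcome. Followed as written, it counts stable pre-existing impairment as incident, which overstates incidence and dilutes the odds ratio towards 1. Survival and its sample size are untouched.

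The overlap between eligibility and threshold rests on the protocol's wording plus a standard eGFR equation, and is secure. The amount of dilution is illustrative only: it depends on the unknown share of patients entering above 133 µmol/L and on assumed admission and event rates, and could be small if investigators exclude most such patients. It merits correction because the remedy uses data already collected.

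**What to change.** Before the first unblinded analysis, define the outcome as new renal dysfunction: an in-hospital creatinine above 133 µmol/L after randomisation, in patients whose screening creatinine was at or below 133. Stating that the value must follow randomisation matters because inpatients are recruited, and the current wording does not exclude earlier values from the recruiting admission. Report patients with a baseline above 133 separately.

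Add a sensitivity analysis that also requires a prespecified relative rise over baseline, to address isolated values. A 1.5-fold rise is one option among several; the choice matters less than fixing it in advance.

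The cost is wording only, since screening creatinine is already scheduled. The downsides are a slightly smaller analysis set, fewer counted events, and some misclassification where the screening value was transiently abnormal.

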#### Participant timeline {13}

The assessments and interventions required at screening, randomisation, and follow-up visits are outlined in Table 2. Eligible patients will be randomised using the secure randomisation website, Sealed Envelope® (www.sealedenvelope.com), which generates anonymised kit codes for trial staff to identify the correct trial medication for the patient, whilst maintaining blinding. Patients should start taking the trial medication as close as possible to the randomisation date (for those enrolled as outpatients) or as soon as they are well enough after discharge from the hospital (for those enrolled as inpatients). Follow-up visits by contact at the outpatient appointment will be on day 10, then at outpatient appointments or by telephone at month 1 and 3-monthly thereafter for 18 months. At month 19, there will be an end-of-study safety telephone call as this marks the end of the treatment period for the trial and denotes the minimum follow-up period. Patients that finish the treatment period prior to the end of the trial will be followed up 6-monthly until the end of the trial.

**Table 2 Tab2:** Trial schedule of interventions and assessments

Visit number	Visit 1		Visit 2	Visit 3	Visit 4	Visit 5	Visit 6	Visit 7	Visit 8	Visit 9	Safety call	Long term follow-up
	(< 12 weeks from randomisation)	Month 0	Day 10	Month 1	Month 3	Month 6	Month 9	Month 12	Month 15	Month 18	Month 19	Every 6 months from month 24 to the end of the trial
	Screening	Randomisation	Follow-up									
Eligibility screening	X											
Informed consent	X											
Medical history	X											
Pregnancy test (*if applicable*)	X^a^											
Ascitic fluid analysis	X^b^											X
Blood tests, liver and renal function tests^c^	X		X^e^		X	X	X	X	X	X		X
Randomisation		X										
Adverse events review			X	X	X	X	X	X	X	X	X	X
Hospital admission review			X	X	X	X	X	X	X	X		X
Concomitant medication review	X		X		X	X	X	X	X	X		X
MARS Questionnaire					X	X	X	X	X	X		
EQ-5D-5L Questionnaire		X				X		X		X		
Dispense trial medication^d^		X			X	X	X	X	X			

^a^Pregnancy test must be completed within 2 weeks prior to randomisation

^b^Ascitic fluid analysis can be done within 12 weeks prior to randomisation

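### MELD progression is taken at the end of trial follow-up (18 to 48 months by entry date), so it can be measured only in those still alive then, and a survival benefit would tilt the comparison against co-trimoxazole

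*Protocol article*

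**What the plan says.** Outcomes {12} lists, as a secondary outcome, progression of liver disease assessed by "an increase in Model for End-Stage Liver Disease (MELD) score between baseline and end of trial" follow-up. In the same list, eight other secondary outcomes carry an explicit 18-month time: admission rates, C. difficile diarrhoea, other infections, cirrhosis events, resistance, transplantation, resolution of ascites and TIPS.

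Sample size {14} states that "the follow-up time will be 18 months minimum with a maximum potential follow-up of 48 months" and that "The recruitment will be uniform over a period of 2.5 years". The end of follow-up therefore depends on when a patient entered.

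Statistical methods {20a} analyses "continuous outcomes using linear regression adjusting for baseline values (i.e. ANCOVA"). Only one outcome is given a multilevel model: "Quality of life scores will be compared using a hierarchical linear regression model".

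Table 2 in Participant timeline {13} schedules bloods at screening, day 10, every 3 months from month 3 to month 18, and then "Every 6 months from month 24 to the end of the trial". Treatment lasts 18 months.

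**The concern.** The time point is stated, and it is a poor one for two reasons.

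First, it is not a common time. One patient's final MELD falls at month 18, as treatment ends. Another's falls at month 48, which is 48 − 18 = 30 months after treatment stopped. The average change has no clear meaning.

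Second, a MELD score at trial close cannot be taken in a patient who has died. The later the time point, the more patients are gone, and if the drug works more are gone from the control arm. If a high or rising MELD raises the risk of death, the patients removed are the ones who were deteriorating. The control survivors then look healthier than the active survivors, even when the drug does nothing to MELD.

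The distortion would appear exactly when the trial succeeds on its primary outcome. A survival benefit could be published beside apparently faster liver-disease progression on co-trimoxazole.

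**Working it through.** **Inputs from Sample size {14}.** Control survival 66% at 18 months, exponential ("we anticipate 66% survival in the control arm at 18 months"); hazard ratio 0.62 ("In the experimental arm, we expect 77% of patients surviving at 18 months"; 0.66^0.62 = 0.773); accrual uniform over 30 months; follow-up 18 to 48 months; 10% cumulative loss; 432 patients, 216 per arm from the 1:1 allocation; 187 events.

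**Step 1: reproduce the plan's figure.** Schoenfeld: 4 × (1.96 + 1.2816)² / (ln 0.62)² = 42.03 / 0.2285 = 184 events; Freedman gives 191. The stated 187 lies between them. Monthly hazards are λ = −ln(0.66)/18 = 0.02308 for control and 0.62 × 0.02308 = 0.01431 for active. Take loss as exponential, reaching 10% at 48 months: η = −ln(0.9)/48 = 0.00220. Define A(k) = (e^(−18k) − e^(−48k)) / (30k). The probability of an observed death is λ/(λ+η) × [1 − A(λ+η)], which is 0.507 for control and 0.359 for active. Expected events are 216 × (0.507 + 0.359) = 187. The model is the plan's own.

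**Step 2: who is alive at trial end.**
- Control: A(0.02308) = (0.660 − 0.330)/0.6925 = 0.476, about 103 of 216.
- Active: A(0.01431) = (0.773 − 0.503)/0.4294 = 0.628, about 136 of 216.
- With the planned loss, about 96 and 127 remain alive and in follow-up.
- At a fixed 18 months: 143 (66%) and 167 (77%).

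The survival gap is about 15 percentage points at trial end and 11 at month 18.

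**Step 3: time of measurement.** Among those alive at trial end, the mean time is 31.3 months for control and 31.9 for active. If the end instead meant each patient's last contact, deaths included, the mean time would be (1 − share alive)/λ: 0.524/0.02308 = 22.7 months and 0.372/0.01431 = 26.0 months, a gap of 3.3 months.

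**Step 4: size of the distortion.** The documents give no MELD distribution, so these inputs are assumptions: baseline mean 15 (SD 5); mean slope 1 point per year; log-hazard of death 0.08 to 0.16 per current MELD point; baseline hazard set so that control survival is 66% at 18 months; no treatment effect on MELD. Final MELD is regressed on arm and baseline among those alive. The standard error is scaled to 216 × share alive per arm, and the false-positive rate follows from bias divided by standard error.

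| Setting | Spurious difference (points, active worse) | False-positive rate |
|---|---|---|
| Trial end, HR 0.62, slope SD 3/year | 0.6 to 0.8 | 9 to 13% |
| Trial end, HR 0.62, slope SD 1.5/year | 0.2 to 0.3 | 6 to 9% |
| Trial end, HR 0.62, slope SD 1/year | 0.13 to 0.17 | 6 to 8% |
| Trial end, HR 0.80, slope SD 3/year | 0.3 to 0.4 | 6 to 7% |
| Trial end, HR 1, any of these | 0 | 5% |
| Month 18, HR 0.62, slope SD 1.5 to 3/year | 0 to 0.2 | 5 to 7% |

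A simpler model, in which the log-hazard rises by 0.3 to 1.0 per SD of MELD change, agrees on direction: 0.08 to 0.13 SD at trial end against 0.05 to 0.10 SD at month 18.

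**The case against.** Several points can fairly be made for the plan.

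- **Survivors only.** A reader might infer that the plan restricts the MELD analysis to survivors. It does not say so. Nor does it name ANCOVA for MELD in particular; an increase in MELD could be coded yes or no and analysed by logistic regression. How death and transplant enter may be set out in the SAP, which is not shown. This stands, and no fault is charged for that silence. But the time point is in the text, and a trial-end score cannot be measured in the dead under either coding.
- **Unequal times between arms.** A reader might infer that varying times bias the comparison. Randomisation balances entry dates, and survivors' mean times differ by only about 0.6 month. Varying times blur what is estimated and lengthen exposure to death; the bias comes from differential survival. Only under the last-contact reading do times differ materially by arm.
- **EQ-5D.** A reader might extend the point to quality of life. Table 2 fixes EQ-5D at months 0, 6, 12 and 18, the levels of its model are not described, and death may be handled in the SAP or the health economic analysis plan. The documents do not support that extension.
- **Magnitude.** The upper figures need both a wide slope SD and the full hazard ratio of 0.62. This stands, and is why a range is given.

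**Conclusion.** The concern holds for MELD progression. The outcome is tied to a time between 18 and 48 months, and by then about 52% of controls and 37% of the active arm are expected to have died. If the drug improves survival as planned, the comparison is tilted against it by roughly 0.2 to 0.8 points, with about 6 to 13% false positives instead of 5%, for slope SDs of 1.5 to 3 per year. The survival shares follow from the plan's figures alone. The MELD figures rest on assumed inputs; their direction does not change across the settings tried, and the bias disappears when the hazard ratio is 1.

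This concerns one secondary outcome and says nothing against the overall-survival analysis. It is worth correcting because the remedy is cheap and the misleading result would accompany a positive trial.

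**What to change.** Define the outcome as change in MELD from baseline to month 18, using the visit 9 bloods already in Table 2. Its notes list bilirubin, INR, creatinine and sodium. Use the existing 3-monthly values in a repeated-measures model, which also helps where a visit is held by telephone or the month 18 sample is missing. Because month 18 reduces truncation by death but does not remove it, add one sensitivity analysis that counts death as a bad outcome, with transplant handled by a stated rule. A ranked composite or a joint longitudinal-survival model would be possible forms, but neither is required.

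The cost is a change to the outcome wording, with matching SAP text, before any unblinded analysis. No new data are needed. The downside is that MELD values after month 18 become descriptive only.
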